## Abstract

**Background::**

Chronic obstructive pulmonary disease (COPD) is a kind of disease that can be prevented and treated. It is characterized by the progressive limitation of airflow and is one of the most familiar human health barriers worldwide. For our program, the objective is to evaluate the impact of continuous care on the life quality of the COPD patients.

**Methods::**

This study will be implemented from June 2021 to March 2022 at Shandong Chest Hospital. The experiment was granted through the Research Ethics Committee of Shandong Chest Hospital (0029-4651). The criteria for inclusion involves:

The criteria for exclusion contains:

For our research, the result measure is St. George's Respiratory Questionnaire (SGRQ).

**Results::**

Table 1 reflects the comparison results of 2 groups after the intervention.

**Conclusion::**

The continuous care on the basis of the theory of Information, Knowledge, Attitude, and Practice (IKAP) can promote the improvement of life quality in the COPD patients.

Trial registration number: researchregistry 6266.

## Introduction

1

Chronic obstructive pulmonary disease (COPD) is a kind of disease that can be prevented and treated.^[1,2]^ It is characterized by the progressive limitation of airflow and is one of the most familiar human health barriers worldwide.^[3]^ While cardiovascular disease-related mortality has decreased evidently over the past 20 years, the number of COPD-related deaths has nearly doubled and COPD has become the fourth major cause of death in the world.^[4,5]^ In the US, it affects more than 15 million people and more than 210 million people worldwide.^[6]^ At the aim of better understanding and preventing the burden of COPD, the World Health Organization (WHO) has made major efforts of public health, but it forecasts that COPD disease will become the third most familiar cause of death globally by 2030.^[7]^ Bronchitis and emphysema can lead to a daily function loss and can be a growing and huge burden.^[8,9]^ The relevant treatment process includes repeated hospitalization, which brings high economic costs to the countries.

The theory of Information, Knowledge, Attitude, and Practice (IKAP) is a kind of relational theory, which has been utilized via a lot of scholars since the 1960s. The theoretical system primarily includes 4 continuous processes for conduction: the collection of information, knowledge acquisition, attitude formation, as well as the practice generation.^[10]^ The relationship between information, and knowledge, attitude as well as practice is gradual. The theory of IKAP has been utilized to the care of patients with a variety of diseases and has exhibited improved results. Nevertheless, it is rarely utilized to treat the COPD patients. Therefore, we conduct this randomized controlled trial protocol to evaluate the impact of continuous care on the life quality of the COPD patients.

## Methods

2

This study will be implemented from June 2021 to March 2022 at Shandong Chest Hospital. The experiment was granted through the Research Ethics Committee of Shandong Chest Hospital (0029-4651) and recorded in research registry (researchregistry6266). Sequence of random numbers is generated by a computer. Sequentially numbered sealed opaque envelopes are used for the concealment of random numbers. All the patients taking part in our experiment are randomly divided to control or study group, and each group includes 30 patients.

### Inclusion and exclusion criteria

2.1

The criteria for inclusion involves:

(1)patients diagnosed with COPD;(2)patients with expectorant, chronic cough, dyspnea, and other symptoms;(3)patients who volunteered to take part in our study;(4)have the cognitive ability to take part in interviews and fill in questionnaires.

The criteria for exclusion contains:

(1)patients with unstable physical conditions, for instance, congestive heart failure, recent myocardial infarction, acute cerebrovascular diseases, and malignant tumor;(2)suffering from bronchial asthma or bronchiectasis;(3)patients with serious physical dysfunction;(4)patients who are unwilling to offer the informed consent to take part in this experiment.

### Nursing care management

2.2

In control group, all the patients will be given the routine nursing, and the education courses of COPD are conducted every 2 weeks. This contains the topics about the guidance on discharge process, the information on disease factors, lung rehabilitation, and the home oxygen therapy. In addition to routine care, intervention group patients are given continuous care based on the theory of IKAP. The nursing intervention primarily contains:

(1)Information collection: nurses collect the information on the psychological and health status of the patients.(2)Knowledge acquisition: this phase includes the provision of the knowledge associated with healthcare to patients. Other topics contain trying to change the unhealthy lifestyles of patients and explaining the importance of respiratory exercises.(3)Attitude generation: at this phase, the goal of nurses is to encourage all patients to remain positive. And nursing staff continues to study and consolidate the content of pre-discharge education of health. Nurses constantly evaluate the daily behavior and knowledge of patients, collect the data on the patients’ behavior change, and find out the major factors that hinder the behaviors change of patients.(4)Practice formation: in this ultimate stage, the nurse guides patients to develop and then maintain good living habits and keep health. The care team of IKAP discusses a nursing plan with each patient conducts it. This includes the conduction of targeted personal interventions to help the patients form a proper understanding of the diseases, ensure that the patients have a capacity to conduct the programs of health education consciously, and facilitate the change to healthy behavior.

### Outcomes

2.3

For our research, the result measure is the St. George's Respiratory Questionnaire (SGRQ).^[11]^ The questionnaire consists of 70 items divided into 3 dimensions, namely, symptoms, activities, and effects.^[12]^

### Statistical analysis

2.4

Through utilizing the Microsoft Excel 2013, the data is recorded, and the data could be analyzed with IBM SPSS Statistics for Windows, version 20 (IBM Corp., Armonk, NY). And all data are represented via the proper characteristics, for instance, median, mean, and percentage. The categorical variables and continuous variables are respectively analyzed using independent *t* tests and *χ*^2^-tests. *P* value less than .05 indicates that there is statistical significance.

## Result

3

Table 1 reflects the comparison results of 2 groups after the intervention.

**Table 1 T1:** The comparison of patients in the 2 groups after intervention.

Variables	Control group (n = 30)	Study group (n = 30)	*P*
St. George's Respiratory Questionnaire Score			
Impact score			
Symptoms score			
Activity score			
Length of stay			
Complications			

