## Conclusion

5

The continuous care on the basis of the theory of IKAP can promote the improvement of life quality in the COPD patients.

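### SGRQ is compared unadjusted after the intervention, with no baseline SGRQ described for both groups; at 30 per arm this costs precision and leaves chance baseline differences in the estimate

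*Protocol article*

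**What the plan says.** The Methods section states that patients are "randomly divided to control or study group, and each group includes 30 patients", using a computer-generated sequence and sealed opaque envelopes. No stratification is described. The Outcomes section names the SGRQ as the outcome measure, with three dimensions and no assessment times.

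The Result section says "Table 1 reflects the comparison results of 2 groups after the intervention". This is the only planned results table, and its title is "The comparison of patients in the 2 groups after intervention". It has one column per group and a P column. It has no baseline, change, difference or confidence interval column.

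The Statistical analysis section says: "The categorical variables and continuous variables are respectively analyzed using independent *t* tests and *χ*^2^-tests". As worded, the tests are attached to the wrong variable types. That is a separate error; here I take the t test to be the one meant for SGRQ scores. It also says that data will be summarised by measures such as the mean, median and percentage.

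The only early collection of patient status described is in Nursing care management, where "nurses collect the information on the psychological and health status of the patients". This is the first step of the study-group intervention, so the control group has no described equivalent. The Conclusion states that the care "can promote the improvement of life quality in the COPD patients".

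**The concern.** A patient's SGRQ score at follow-up is likely to depend in part on the score at entry. A comparison of follow-up scores that ignores the entry score carries all of the between-patient variance. It also carries forward, in proportion to the correlation, whatever difference between the groups arose by chance at randomisation. With 60 patients and no stratification, such differences need not be small.

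The Conclusion also speaks of improvement. Follow-up scores alone can show that one group ended better than the other. They cannot show that patients in either group got better, worsened less, or stayed as they were.

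This is partly a matter of data collection. If the SGRQ is not completed before the intervention starts, no later analysis plan can recover it.

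**Working it through.** **Inputs from the article.** 30 patients per group (Methods); significance at P below .05 (Statistical analysis), with sidedness not stated and two-sided assumed here; comparison after the intervention only (Result, Table 1); tests without covariates (Statistical analysis).

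**Inputs assumed, because the article gives none.** Baseline to follow-up correlation r = 0.3, 0.5 and 0.7; standardised difference d = 0.5 for illustration; equal variances; no dropout. The article states no power, effect size or SD, so there is no calculation of its own to reproduce. All results are in SD units.

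**Step 1: chance baseline difference.** SE = √(2/30) = 0.258 SD, so the 95% range is ±1.96 × 0.258 = ±0.51 SD. The probability of a difference in either direction is 33% for more than 0.25 SD, 24.5% for more than 0.3 SD, and 5.3% for more than 0.5 SD.

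**Step 2: what an imbalance does to the unadjusted estimate.** The expected shift is r × imbalance.
- Imbalance of 0.25 SD: shift of 0.075, 0.125 and 0.175 SD for r = 0.3, 0.5 and 0.7.
- Imbalance of 0.5 SD: shift of 0.15, 0.25 and 0.35 SD. Given that imbalance, the type I error of the unadjusted test is about 8%, 13% and 20%.
- At 0.25 SD the conditional type I error is 4.9%, 4.7% and 3.6%, so the false-positive risk rises only in the less common, larger imbalances. Averaged over all randomisations it stays at 5%.

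**Step 3: gain from ANCOVA on baseline.** The variance is multiplied by 1 − r². The equivalent number per arm is 30/(1 − r²). The difference detectable with 80% power is (1.960 + 0.842) × 0.258 × √(1 − r²). Power is approximately Φ(d / [0.258 × √(1 − r²)] − 1.960). For d = 0.5 without adjustment, 0.5/0.258 = 1.936, and Φ(−0.024) = 0.49.

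| Analysis | Variance factor | Equivalent n per arm | Detectable at 80% power (SD) | Power at d = 0.5 |
|---|---|---|---|---|
| Follow-up only | 1 | 30 | 0.72 | 49% |
| ANCOVA, r = 0.3 | 0.91 | 33 | 0.69 | 53% |
| ANCOVA, r = 0.5 | 0.75 | 40 | 0.63 | 61% |
| ANCOVA, r = 0.7 | 0.51 | 59 | 0.52 | 77% |

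The variance cuts are therefore 9%, 25% and 49%. Using the noncentral t distribution instead of the normal approximation, power at d = 0.5 is 48% unadjusted and 51%, 59% and 76% adjusted, so the picture does not change.

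**The case against.** Four objections deserve an answer.

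**The comparison is valid as planned.** Randomisation is computer-generated and concealed, and the overall type I error already allows for chance imbalance. This stands. A reader might infer that the result would be biased or the test invalid; the article does not support that. What is lost is precision, together with protection against the particular imbalance that happens to occur.

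**The stated aim is the impact of the care, which is a between-group effect.** A better follow-up score in a randomised study group does support improvement relative to control. This also stands. A reader might infer that follow-up scores can support no claim of improvement at all, which goes too far; only within-patient improvement is out of reach. ANCOVA likewise estimates a between-group contrast. It is the recorded baseline scores that would let change be described.

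**The article is condensed.** An assessment schedule or baseline table may sit in a document not shown, and the article never says that baseline SGRQ will not be taken. That is right, and its absence from the trial cannot be inferred. But the article does more than stay silent: it fixes the time point in the table and names unadjusted tests. A later plan using ANCOVA would depart from it.

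**The size is uncertain, and the plan is not as bare as it may look.** The documents give no correlation, and at r = 0.3 the gain is about 4 percentage points of power. Group summaries are planned as well as P values. The eligibility criteria require symptoms and exclude unstable conditions and serious physical dysfunction, so it would be wrong to say that the patient range is unrestricted. Restriction of range tends to lower r. All of this stands and limits how firmly the gain can be stated.

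**Conclusion.** The point holds as one of precision and chance imbalance. The article fixes an unadjusted comparison of follow-up SGRQ scores and describes no baseline SGRQ in both groups. At 30 per arm, 80% power is reached only for a difference of about 0.72 SD, and a chance baseline difference with standard error 0.26 SD stays uncorrected.

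The gain from adjustment ranges from small (49% to 53% power at d = 0.5 if r = 0.3) to large (49% to 77% if r = 0.7). That range rests on assumed r and d, a two-sided 5% level and no dropout. The description of the plan is certain; the size of the loss is not. The change is worth making because it is cheap and must be in place before patients are allocated.

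**What to change.** 1. State in the Outcomes section that every patient in both groups completes the SGRQ after consent and before the envelope is opened, separately from the information gathering that belongs to the study-group intervention.
2. State in the Statistical analysis section that follow-up SGRQ will be analysed by a linear model with group and baseline SGRQ as terms (ANCOVA).
3. Add to Table 1 the baseline SGRQ by group and the adjusted mean difference with its 95% confidence interval, so that a non-significant P value can be read against the range of effects still compatible with the data.
4. Word the conclusion as a difference between groups at follow-up. Describe change within patients only from the recorded baseline scores.

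The cost is one extra completion of a questionnaire already in use, for 60 patients, and one model in the statistical software already named. The small downside is patient time.

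### The SGRQ is the only named outcome, but the score that carries the conclusion is not fixed, and Table 1 plans P values for five or six rows

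*Protocol article*

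**What the plan says.** **Outcome (section 2.3; the Abstract agrees).** "For our research, the result measure is the St. George's Respiratory Questionnaire". The section adds that the questionnaire is "divided into 3 dimensions, namely, symptoms, activities, and effects". It does not say whether the total or one of the three domain scores is to be compared.

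**Results shell (section 3, Table 1).** The table, still empty, is captioned "The comparison of patients in the 2 groups after intervention". Beside a P column it lists "St. George's Respiratory Questionnaire Score", then impact, symptoms and activity scores, then "Length of stay" and "Complications". The last two appear neither in section 2.3 nor in the stated objective, which is quality of life.

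**Decision rule (section 2.4).** A P "value less than .05 indicates that there is statistical significance". The rule is not restricted to one variable, and no row is called primary.

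**Conclusion (section 5 and the Abstract).** The claim concerns improved quality of life only.

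**The concern.** Two things do not fit together.

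1. The outcomes section and the results table list different outcomes. The section has one measure. The table adds length of stay and complications.
2. The one named measure yields several scores, and the text does not say which one decides. If the SGRQ line in Table 1 is a total, four SGRQ scores are tested. If it is only a heading, three are tested and the total is never compared.

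Under the rule in section 2.4, a single domain below .05 would count as significant and could be presented as support for the quality-of-life conclusion even if the other SGRQ scores showed nothing. The error rate behind that conclusion would then not be the 5% that the threshold suggests.

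**Working it through.** The article gives no power, sample-size basis or overall error rate, so there is no figure of its own to reproduce beyond the per-test .05.

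**Inputs from the article**
- Threshold .05 per test (section 2.4).
- 30 patients per group (section 2, Methods).
- Three SGRQ domains (section 2.3).
- Table 1 rows: three domains, plus possibly a total, plus length of stay and complications. That makes three or four SGRQ tests and five or six tests in all.

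**Assumptions not in the article**
- Two-sided tests: t tests for continuous rows and a chi-square test for complications.
- Equal correlation between SGRQ domains, varied from 0.4 to 0.9.
- Total score a mean or weighted sum of the domains.
- Complication rate 20%.
- Length of stay and complications either independent of the SGRQ or correlated 0.3 with it.

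**Step 1: independent tests.** The chance of at least one false positive in k tests is 1 − 0.95^k.
- k = 3: 1 − 0.95³ = 14.3%
- k = 4: 1 − 0.95⁴ = 18.5%
- k = 5: 1 − 0.95⁵ = 22.6%
- k = 6: 1 − 0.95⁶ = 26.5%

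The values for four and six tests are ceilings only, because a total built from the domains cannot be independent of them.

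**Step 2: SGRQ scores only, correlated.** Simulation of 40,000 trials with no treatment effect, 30 per group:

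| Domain correlation | 3 domains | 3 domains + total | False benefit (3 / 4 scores) |
|---|---|---|---|
| 0.4 | 13.1% | 13.7% | 6.5% / 6.9% |
| 0.6 | 11.6% | 11.9% | 5.8% / 6.0% |
| 0.7 | 11.1% | 11.2% | 5.6% / 5.7% |
| 0.9 | 8.5% | 8.5% | 4.2% / 4.2% |

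A separate simulation of 20,000 trials gave 14.0%, 12.3% and 11.2% for four scores at correlations 0.4, 0.6 and 0.7. Together these give about 8-14% in either direction and about 4-7% for false benefit. A single two-sided test gives 5% and 2.5%.

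**Step 3: all rows of Table 1.** Simulation of 40,000 trials:

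| Domain correlation | Other two rows independent (5 / 6 rows) | Other two rows correlated 0.3 (5 / 6 rows) |
|---|---|---|
| 0.5 | 21.1% / 21.2% | 20.6% / 20.6% |
| 0.7 | 19.8% / 19.7% | 18.6% / 19.1% |
| 0.9 | 17.1% / 17.1% | 16.9% / 16.8% |

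With the independent ceilings of 22.6% and 26.5% from step 1, the range is about 17-26%. At the correlations examined, five and six rows differ by little, so the result hardly depends on how the SGRQ line is read.

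**Step 4: with one score named.** A single pre-named SGRQ score tested at .05 returns the error for the main claim to 5%. If all rows stayed co-equal, a Bonferroni rule would need .05/5 = .01 or .05/6 = .0083 per row.

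**The case against.** Four arguments can be made on the other side.

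- **This is a condensed article.** Multiplicity rules and the handling of domain scores are often left to a full protocol or analysis plan, and neither is shown. That stands as far as a missing adjustment method goes, and none is criticised here. It does not remove the disagreement between section 2.3 and Table 1, since both are stated in this document.
- **The SGRQ is named in the singular.** It can fairly be read as the primary outcome in all but name, with the other rows supportive. That is a reasonable reading of the instrument's status, but it does not say which SGRQ score is tested.
- **The SGRQ line may be a total.** The layout of the table is lost in the text at hand, so its status cannot be settled. The point does not depend on it: three scores and four scores give nearly the same error.
- **The threshold sentence is generic.** It does not say that every row is confirmatory. True, but nothing in the text marks any row as not confirmatory.

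A reader might also infer that the quality-of-life claim itself carries an error of about 20%, or that any of the five or six rows could support it. The document does not support that. The objective and the conclusion concern quality of life only, and neither length of stay nor complications measures it. The figure of about 20% also counts false results in both directions, and false benefit is roughly half of any such figure.

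**Conclusion.** The point holds in a limited form. Section 2.3 and Table 1 disagree on the outcomes, and the SGRQ score that carries the conclusion is not fixed. For the quality-of-life claim, the chance of at least one false-positive SGRQ result is about 8-14% instead of 5%, or about 4-7% instead of 2.5% for false benefit. Across all rows of the table it is about 17-26%, but that larger figure describes the table and not the trial's conclusion.

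The mismatch can be read directly from the text. The percentages are less certain: they rest on assumed domain correlations, two-sided tests, an assumed complication rate and no true effect on any outcome. If the sponsor confirms that one particular SGRQ score is the sole basis for the conclusion, the error for that claim is 5% and only the alignment of the two sections remains to be done.

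**What to change.** - **Section 2.3:** name one SGRQ score, naturally the total, at one fixed time as the single primary outcome, tested at two-sided .05 and the sole basis for the conclusion.
- **Section 2.3 and Table 1:** label the domain scores, length of stay and complications as secondary in both places.
- **Table 1:** give the primary score an explicit row of its own, so that it cannot be taken for a heading.
- **Section 2.4:** state that secondary rows do not on their own prove benefit. Descriptive reporting with estimates and 95% confidence intervals, testing the domains only if the primary is significant, or a multiplicity adjustment are all acceptable. The choice should be made before the data are seen.

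**Cost:** wording only, with no added patients or visits. The downside is that a favourable domain or secondary result can no longer support a claim of benefit by itself.

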## Discussion

4

The dyspnea, low exercise tolerance, and mood disorders have formerly been demonstrated to affect the health status and life quality of patients with COPD.^[13–15]^ The theory of IKAP is beneficial to all these problems. The theoretical system of IKAP primarily includes 4 continuous processes for conduction, namely, the collection of information, knowledge acquisition, attitude formation, as well as the practice generation that encourage all the patients to abide by the plans of health education consciously and facilitate the changes of health behaviors.^[16]^ For this experiment, the innovations can be summed up in the use of the theory of IKAP in the continuous care of patients with COPD. Therefore, our research team has developed a set of planned, comprehensive, and continuous program of nursing intervention to help the patients understand the etiology, symptoms, and treatment in a real-time and comprehensive manner. This kind of intervention can enhance the confidence and attitude of patients to adhere to healthy behavior, and can guide the occurrence of behavior conducive to rehabilitation. The high-quality randomized controlled researches remains needed in-depth research.

